## We will interview a purposive sample of ambulance clinicians in EMAS who delivered the intervention and patients with hypoglycaemia who were attended in the geographical areas following introduction of the intervention using maximum variation in characteristics such as practitioner age, sex and geographical region and patient age, sex, and geographical region. For the patient sample we will also include patients who did or did not experience a recurrent hypoglycaemic episode as part of the intervention. We will include approximately 10-15 staff and 10-15 patients until we achieve theoretical saturation.

## DATA ANALYSIS

WP1 Stepped wedge: Dispatch data will be linked with clinical data using a unique job number. People included will be identified and tracked for repeat attendances. In the stepped wedge design, the intervention and control observation periods take the place of the treatment and control groups in a parallel trial and the distribution of results across unexposed observation periods is compared with that across the exposed observation periods. There are a small number of steps and so characteristics of the groups in the wedge can be compared by group, including number, the average cluster size, cluster characteristics, and important patient characteristics.

Following an intention-to-treat principle, clusters will be analysed according to their crossover time irrespective of whether crossover was achieved at the desired time. Under the stepped wedge design the evaluation happens over a period of time, during which the number of clusters exposed to the intervention gradually increases. This means that unexposed observations will, on average, be from an earlier calendar time than exposed observations. Additionally, policy and service delivery changes may occur. Calendar time is associated with both the exposure to the intervention and also possibly the outcome, and so is a potential confounder and will be adjusted for in the analysis.

A linear mixed model will be fitted adjusting for the systematically different observation periods and for clustering in the data. Time is included as a fixed effect and a random effect for cluster. The design also allows examination of the impact of the intervention changing over time once it is introduced into a cluster.

WP2 Health economics: We will use a cost consequences model, estimating costs from NHS Reference Costs to evaluate the costs of the intervention in relation to its effects. Key cost drivers associated with repeat hypoglycaemic episodes will be modelled.

WP3 Survey: We will analyse the overall experience of both patients and ambulance staff, as well as use descriptive statistics and comparisons between responder groups (e.g. ambulance staff vs patients; paramedics vs emergency medical technicians), where appropriate.

WP4 Qualitative: Qualitative data analysis will involve thematic coding of collected data (i.e. framework analysis) and the audio recorded data (transcribed verbatim) will be entered into NVivo 12 qualitative data analysis software to facilitate analysis. We will use the Medical Research Council guidance on process evaluations of complex interventions^2^ as a framework to guide the analysis and synthesis of our data, complemented by inductive codes to ensure all aspects of the participants’ experience are fully captured. Accordingly, our framework will be developed based on the following key components and functions of a process evaluation: description of the intervention and its causal assumptions; the implementation process (how delivery was achieved, training, resources, etc.) and what was delivered (fidelity, adaptations, etc.); the mechanisms of impact (participant responses to and interactions with the intervention, mediators, unexpected pathways and consequences), context (contextual factors that shape theories of how the intervention works and that affect the implementation, intervention mechanisms, etc.); and outcomes.

WP5 Integration: We will integrate qualitative and quantitative data to explain the findings from the stepped wedge and economic evaluation using the interview and survey findings.

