**Description of the intervention**: The “Hypos can strike twice booklet” has a section where the paramedics record for the patient a summary of their physical condition both when the ambulance service arrives and when it departs. It also includes a section where the ambulance staff record details of the relevant treatment provided. We hope this will be useful to patients who may be confused during their hypos (and hence during the visit from the ambulance service) so that they can refer back to it later after their recovery. All patients receiving the booklet will be advised to seek further advice from their GP or local community diabetes services so that they have an opportunity to review with a health professional whether they require any changes in their usual diabetic medication/insulin. In addition to explaining to the patients what has happened to them, the booklet also provides advice about what to eat following a hypo and reminds them to avoid strenuous activities, alcohol and be cautious about driving during the first few hours of recovery. It also encourages them to undertake regular self-monitoring of their blood-glucose levels. FAQs are provided to explain in lay terms, what hypos are, the symptoms, causes, how to try to prevent them and what to do if they happen again. We hope that patients will find the booklet reassuring and serve as a useful and easy-to-read resource for them. It is hoped that this intervention will reduce the chances of the patients having further severe hypos and reduce ambulance attendances for this.

The ‘Hypo’s can strike twice’ intervention was delivered in successive county areas of East Midlands Ambulance Service NHS Trust (EMAS). Communications face-to-face, email and information publicised on an electronic bulletin (E-news), twitter and Facebook, advise staff to implement the booklet when visiting patients with diabetes who have experienced hypoglycaemia. Reminders are also provided to staff to complete the care bundle for hypoglycaemia and to refer patients to an appropriate healthcare professional following an episode of hypoglycaemia.

The intervention was rolled out by division (county) in EMAS in the following steps:

Step 1: October/November 2018, Leicester and Northamptonshire.

Step 2: January/February 2019, Nottinghamshire and Derbyshire.

Step 3: April/May 2019, Lincolnshire.

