# STUDY DESIGN

Non-randomised stepped wedge design with mixed methods process evaluation.

Work package (WP) 1 Stepped wedge: We will use routine anonymised data from routine call-and-dispatch and clinical records data from EMAS for 12 months before the intervention was first introduced (September 2017) to at least 6 months after the final step of the introduction in April 2019, i.e. October 2019. We will include call categories, timings, geographical location, together with demographic (age, sex) and clinical information, physiological measurements taken, treatments given, and whether the patient was referred to community services (general practitioner, community diabetes nurse or alternative) for their diabetes or transported to hospital by ambulance. Hypoglycaemia is recorded in electronic clinical records under ‘chief complaint’ or impression’ which will enable us to identify incidents of patients presenting with hypoglycaemia. Individual patients will be assigned a unique (non-personally identifiable) number in the anonymised dataset provided to the university which will enable us to identify repeat attendances for an individual patient.

WP2 Health economics: We will use a cost-consequences approach to estimate the costs of the intervention in relation to its effects. Total costs will be estimated, from an NHS perspective, using unit costs from NHS Reference Costs, Emergency Services Reference Costs, and other relevant costs, multiplied by resource units.

WP3 Survey: We will use a self-administered survey to understand implementation, mechanisms of impact, and contextual factors. We will use random sampling to select patients with hypoglycaemia who were attended stratified by geographical area, from the ambulance service user records and we will send them questionnaires by post (with a stamped addressed envelope for return to the University of Lincoln) or offer them the option to complete the questionnaire on-line, according to their preference. We will conduct an online survey to all front-line clinicians to assess attitudes, perceptions and behaviour towards the intervention including the booklet. We will also conduct a self-administered postal questionnaire to patients using a Patient Reported Experience Measure, previously developed and validated by [name] and colleagues^19 20^. The sample size calculation for the survey is included below.

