### Sampling

### Size of sample

WP1 and 2 Stepped wedge (non-randomised control design):

3 clusters at county level (1.Leicestershire+Northamptonshire; 2.Derbyshire+Nottinghamshire; 3.Lincolnshire) implementing intervention at each time step lasting around 3 months, so 12 data collection periods (one collection per cluster per time step).

Primary outcome: Proportion of repeat ambulance calls and attendances for hypoglycaemia within 14 days.

Significance level = 0.05

Intraclass coefficient = 0.1 (conservative estimate)

The number of hypo calls per time period (3 months) per county group was estimated from routine data from EMAS for years 2012-2017 (6 years).

| **County group** | **Frequency** | **Percentage** |
| --- | --- | --- |
| Leicestershire | 639,811 | 19.39 |
| Northamptonshire | 449,916 | 13.63 |
| Derbyshire | 662,745 | 20.08 |
| Nottinghamshire | 773,066 | 23.43 |
| Lincolnshire | 774,128 | 23.46 |
| Total | 3,299,972 | 100.00 |

Number of hypos expected every 3 months = 1% of attendances

Leicestershire Northamptonshire = (639811+449916)*0.01*(1/24) = 454

Derbyshire Nottinghamshire = (662745+773066)*0.01*(1/24) = 598

Lincolnshire = (774128)*0.01*(1/24) = 323

Proportion pre-intervention with a repeat attendance = 0.1

Power is fixed at 80%.

The detectable difference is a reduction of repeat attendances of 5% (i.e. from 10% to 5%).

WP3 Survey: We will survey all front-line staff. We will survey patients who received the intervention based on a response rate of 20% from a previously published study using the Ambulance Patient Reported Experience Measure.^19 20^ In this study the experience measure included 3 components AmbCallScore (mean 62.37, standard deviation 26.7), AmbCareScore (mean 85.6, standard deviation 16.4) and AmbLeaveScore (mean 73.77, standard deviation 21.6) Assuming the proportion of sample with the expected outcome: 0.50, margin of error: +/- 10.0%, confidence level: 95.0%, the estimated sample size required is 96. The estimate adjusted for a 20% response rate is 447. This means sampling from 447 we anticipate an estimate of each of the scores that is within 10% of the true value.

WP4 Qualitative; The qualitative sample of 10-15 staff and 10-15 patients is based on previous experience of the sample required to achieve theoretical saturation.

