**RANDOMISATION AND BLINDING**

This study will not involve randomisation or blinding of participants or study personnel.

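### Cluster is a random effect in a roll-out that was not randomised, so stable differences between early and late county groups can enter the intervention effect; fixed county indicators close that route cheaply

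*Protocol*

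**What the plan says.** The Protocol's STUDY DESIGN section describes a "Non-randomised stepped wedge design with mixed methods process evaluation", and RANDOMISATION AND BLINDING confirms: "This study will not involve randomisation or blinding of participants or study personnel". STUDY BACKGROUND and RATIONALE gives the order of introduction, from "Step 1: October/November 2018, Leicester and Northamptonshire" to "Step 3: April/May 2019, Lincolnshire", with Nottinghamshire and Derbyshire in between. Size of sample treats these as "3 clusters at county level".

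Under DATA ANALYSIS the model is stated as: "A linear mixed model will be fitted adjusting for the systematically different observation periods and for clustering in the data". The next sentence gives its terms: "Time is included as a fixed effect and a random effect for cluster". The STUDY SUMMARY repeats both sentences. No fixed county term and no adjustment for baseline differences between counties is stated. The same section does plan to compare the groups' characteristics, but that is descriptive and adjusts nothing.

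**The concern.** A random cluster intercept is valid for the intervention effect only if the cluster's level is independent of when it crosses over. In a randomised stepped wedge the random order secures this. Here nothing does.

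When the assumption fails, the estimator mixes two comparisons: the change within each county group, and the contrast between exposed and unexposed groups in the same period. The second carries stable county differences into the effect. Its weight grows as the estimated between-county variance shrinks, and that variance comes from three groups only. This happens even if all counties move exactly in parallel and a single intercept per group is the correct variance structure.

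The protocol's own argument points the same way. It adjusts for calendar time as a potential confounder because time is linked to exposure and possibly to outcome. County group determines the length of exposure and may also be linked to outcome, yet it is handled only as clustering. If the early counties simply have lower repeat rates, part of that gap is reported as benefit; if higher, as harm.

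**Working it through.** **Inputs from the Protocol (Size of sample):** three groups, steps of about 3 months, 3 × 4 = 12 cells; alpha 0.05 (two-sided assumed); ICC 0.1; control rate 10%; target 10% to 5%; 80% power. **From STUDY DESIGN:** data from September 2017 to October 2019, which is 4 + 12 + 10 = 26 months. **Assumed, because the documents are silent:** county-specific repeat rates.

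**1. The plan's own figures.** Cell sizes reproduce: 1,089,727 × 0.01/24 = 454; 1,435,811 × 0.01/24 = 598; 774,128 × 0.01/24 = 323. With fixed period effects, a random cluster intercept and variance 0.1 × 0.9 = 0.09, using 323 in every cell gives a detectable difference of 4.85 points and 82.3% power for 5 points, close to the stated 80%. The three listed sizes give 4.2 points and 91.6%.

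**2. How much of a stable county difference leaks in.** The generalised least squares estimate is a weighted sum of cell proportions, Σ w(k,t)·y(k,t). A stable shift δ(k) in group k adds L(k)·δ(k), where L(k) = Σ over t of w(k,t). On the 4-period grid with cells 454/598/323, for shifts of +2/0/−2 points in step order:

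| ICC used in fitting | L first / middle / last | Bias (points) |
|---|---|---|
| 0.1 | +0.006 / 0 / −0.006 | 2 × (0.006 + 0.006) = 0.02 |
| 0.01 | +0.063 / 0 / −0.062 | 2 × (0.063 + 0.062) = 0.25 |
| 0.001 | +0.354 / −0.017 / −0.337 | 2 × (0.354 + 0.337) = 1.38 |
| 0 | +0.745 / −0.103 / −0.642 | 2 × (0.745 + 0.642) = 2.77 |
| County fixed | 0 / 0 / 0 | 0 |

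The planning ICC implies a between-county SD of √(0.1 × 0.09) = 0.095, or 9.5 points around a 10% rate. The analysis will use an estimated variance, not 0.1.

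**3. With the variance estimated by REML.** Simulation with no true effect, parallel time and group levels of −d, 0, +d in roll-out order. The 26-month grid has crossovers after months 13, 16 and 19. Negative bias is spurious benefit.

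| d (points) | 26 months: bias | 26 months: false positives | 12 cells: bias | 12 cells: false positives |
|---|---|---|---|---|
| 0.5 | −0.47 | 6.2% | −0.47 | 7.6% |
| 1 | −0.44 | 7.0% | −0.72 | 11.5% |
| 2 | −0.23 | 5.6% | −0.61 | 11.2% |

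With fixed county effects the bias was at most 0.10 points in every setting and rejection 4.2% to 5.4%. Repeat runs on 26 months gave false-positive rates of 6.0%, 8.3% and 6.1% at d = 0.5, 1 and 2, and 5.3% at d = 3. The county variance was estimated as zero in 41%, 9% and none of those fits at d = 0.5, 1 and 2. On 12 cells it was zero in 57%, 38% and 5%. A 12-cell run at d = 1.5 gave 0.78 points and 13.7%.

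**4. Other patterns, 12 cells, no true effect.**
- Middle group +2 points: bias −0.03, rejection 4.5%.
- Levels +1/−1/+1: bias 0.04, rejection 5.0%.
- Monotone ±5 points: bias 0.28, rejection 5.0%.

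The problem therefore needs a gradient in step order, within a limited range of sizes.

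**The case against.** The strongest reply is that at the planning ICC of 0.1 only about 0.6% of a county difference leaks in, so there is nothing to correct. That is arithmetically right, but it cuts both ways. If 0.1 were true, fixed effects would cost nothing either: the variance ratio is 1.003 and power 91.5% against 91.6%. If county differences are of the order of 1 or 2 points instead of 9.5, the estimated variance is small and the leakage is not negligible.

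Three stronger readings are tempting, and the documents do not support them.
- A reader might infer that the ambulance service picked the order with baseline rates in view. The protocol says only that roll-out was by division and not randomised. Nothing links the order to the repeat rate.
- A reader might take the 12% false-positive rate as the expected figure. It belongs to the 12-cell planning grid. The data to be analysed span 26 months, where the inflation is modest.
- A reader might conclude that the bias is certain. It depends on a step-ordered gradient that no figure in the protocol shows or rules out.

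It also stands that the change trades bias against variance. On 12 cells the random-effect model has the smaller root mean squared error when counties do not differ (1.36 against 1.60 points) and at d = 0.5 (1.45 against 1.60). On 26 months the two are about equal at d = 0.5 (1.37 against 1.35).

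**Conclusion.** The point holds as a conditional weakness in the stated model. The protocol fixes, in two places, a cluster term whose validity depends on an independence that the non-randomised design does not provide. The SAP is not at hand and may already say otherwise.

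On the 26-month data, if repeat rates follow step order by 0.5 to 2 points per group, expect about 0.2 to 0.45 points of bias and a false-positive rate of about 6% to 8%. On the 4-period planning grid the figures reach roughly 0.75 points and 12%. The 26-month bias is under a tenth of the 5-point target. With differences out of step order, or as large as ICC 0.1 implies, it is negligible. All figures assume parallel time trends, normal-theory tests and hypothetical county rates. The mechanism is certain; the size in this trial is unknown. The point is a cheap improvement and does not invalidate the design.

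**What to change.** In DATA ANALYSIS and in the matching row of the STUDY SUMMARY, replace the random effect for cluster with fixed indicators for county group (or for county), alongside the fixed calendar-period effects. The intervention effect then rests on change within each county group compared with the other groups over the same periods.

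The edit is one sentence in each place and needs no new data. If counties truly do not differ, the standard error rises by about 4% to 7% on the 26-month data (root mean squared error 1.39 against 1.30 points, a ratio of 1.07) and by up to about 20% on the 12-cell grid. At ICC 0.1 the cost is close to zero. The change does not remove time trends that differ between counties, and the protocol should say so as a remaining limitation.

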## STUDY SETTING

This is a single centre study. All participants will be recruited from routine call-and-dispatch and clinical records data from East Midlands Ambulance Service NHS Trust.

# SELECTION OF PARTICIPANTS

## ELIGIBILITY CRITERIA

Ensure consistency with A15 IRAS

### Inclusion Criteria

**Patients**

Young adults aged 16-17 years and adults aged 18 years+ with diabetes experiencing hypoglycaemia needing an ambulance service response. Hypoglycaemia for this study was identified as a ‘clinical impression’ of ‘hypoglycaemia’ or ‘diabetic problem’. Hypoglycaemia may also be identified according to ambulance guidelines^1^ as any blood glucose less than 4mmol/L.

**Clinicians**

Ambulance staff providing treatment and advice to people who have had a hypoglycaemic attack.

### Exclusion Criteria

**Patients**

Children under the age of 16 years.

**Clinicians**

Ambulance staff providing treatment and advice for incidents other than hypoglycaemia.

### Sampling

### Size of sample

WP1 and 2 Stepped wedge (non-randomised control design):

3 clusters at county level (1.Leicestershire+Northamptonshire; 2.Derbyshire+Nottinghamshire; 3.Lincolnshire) implementing intervention at each time step lasting around 3 months, so 12 data collection periods (one collection per cluster per time step).

Primary outcome: Proportion of repeat ambulance calls and attendances for hypoglycaemia within 14 days.

Significance level = 0.05

Intraclass coefficient = 0.1 (conservative estimate)

The number of hypo calls per time period (3 months) per county group was estimated from routine data from EMAS for years 2012-2017 (6 years).

| **County group** | **Frequency** | **Percentage** |
| --- | --- | --- |
| Leicestershire | 639,811 | 19.39 |
| Northamptonshire | 449,916 | 13.63 |
| Derbyshire | 662,745 | 20.08 |
| Nottinghamshire | 773,066 | 23.43 |
| Lincolnshire | 774,128 | 23.46 |
| Total | 3,299,972 | 100.00 |

Number of hypos expected every 3 months = 1% of attendances

Leicestershire Northamptonshire = (639811+449916)*0.01*(1/24) = 454

Derbyshire Nottinghamshire = (662745+773066)*0.01*(1/24) = 598

Lincolnshire = (774128)*0.01*(1/24) = 323

Proportion pre-intervention with a repeat attendance = 0.1

Power is fixed at 80%.

The detectable difference is a reduction of repeat attendances of 5% (i.e. from 10% to 5%).

WP3 Survey: We will survey all front-line staff. We will survey patients who received the intervention based on a response rate of 20% from a previously published study using the Ambulance Patient Reported Experience Measure.^19 20^ In this study the experience measure included 3 components AmbCallScore (mean 62.37, standard deviation 26.7), AmbCareScore (mean 85.6, standard deviation 16.4) and AmbLeaveScore (mean 73.77, standard deviation 21.6) Assuming the proportion of sample with the expected outcome: 0.50, margin of error: +/- 10.0%, confidence level: 95.0%, the estimated sample size required is 96. The estimate adjusted for a 20% response rate is 447. This means sampling from 447 we anticipate an estimate of each of the scores that is within 10% of the true value.

WP4 Qualitative; The qualitative sample of 10-15 staff and 10-15 patients is based on previous experience of the sample required to achieve theoretical saturation.

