# STUDY BACKGROUND and RATIONALE

Diabetes is increasing in prevalence, now affecting 5% of UK adults^3^. Efforts to improve diabetes control, using insulin and drugs to reduce complications, have led to increased rates of hypoglycaemia in people with diabetes^4^. Interruption of glucose supply to the brain causes cerebral dysfunction which, unless corrected promptly, can cause cognitive impairment, confusion, coma and, if prolonged, death.

Hypoglycaemia, a common adverse complication of diabetes treatment^5^, is often managed by patients themselves or their relatives, but severe hypoglycaemia (defined as cognitive impairment severe enough to require external assistance for recovery) frequently requires an ambulance resulting in Emergency Department attendance or hospital admission^6^. Severe hypoglycaemia constitutes around 1% of 1.7 million emergency ambulance calls in England and Scotland resulting in 100 thousand paramedic attendances and estimated costs in England of £13.6 million annually^7^.

Hypoglycaemia is associated with adverse consequences including higher mortality, morbidity and health service costs due to hospital attendance/admission^8 9 10^. It is also frightening for both patients and relatives and impairs quality of life and productivity, leading to poor long term control^11 12^.

A common accompaniment of insulin treated diabetes is impaired awareness (affecting around 25% of adults with type 1 and 10% of type 2 diabetes) when people experience reduced symptoms without having or recognising warning signs of impending hypoglycaemia. It increases the chance of a subsequent severe hypoglycaemic event by threefold^13^. Impaired awareness is more common in those who call an ambulance for hypoglycaemia with around half of type 1 diabetes individuals displaying features of reduced awareness^14^.

A systematic review highlighted that those with hypoglycaemia attended by ambulance services frequently have recurrent episodes, do not attend primary care when advised to do so by ambulance staff, but often require changes in therapy to prevent further episodes^15^. Recurrent hypoglycaemic episodes following ambulance calls are estimated to occur in 7.7% at 3 months and 17.7% at 6 months (data from Scottish Ambulance Service). The authors of the systematic review recommended development and evaluation of community referral pathways for hypoglycaemia^15^.

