# OUTCOME MEASURES/ENDPOINTS

## PRIMARY OUTCOME MEASURE/ENDPOINT

Repeat ambulance calls and attendances for hypoglycaemia within 14 days.

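### The 10% baseline behind the 14-day power statement has no source and exceeds the only recurrence rate the protocol cites (7.7% at 3 months)

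*Protocol*

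**What the plan says.** The primary endpoint is "Repeat ambulance calls and attendances for hypoglycaemia within 14 days". The sample-size section for the stepped wedge repeats that window ("Primary outcome: Proportion of repeat ambulance calls and attendances for hypoglycaemia within 14 days") and then lists its inputs: "Significance level = 0.05"; "Intraclass coefficient = 0.1 (conservative estimate"); "Power is fixed at 80" per cent; and "Proportion pre-intervention with a repeat attendance = 0.1". It concludes: "The detectable difference is a reduction of repeat attendances of 5% (i.e. from 10% to 5" per cent).

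The same section uses the ambulance service's 2012–2017 routine data to derive call volumes (454, 598 and 323 hypoglycaemia calls per quarter in the three county groups). It does not say where the 0.1 comes from.

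The background section gives the protocol's only empirical recurrence rates: "Recurrent hypoglycaemic episodes following ambulance calls are estimated to occur in 7.7% at 3 months and 17.7% at 6 months". It attributes them to the Scottish Ambulance Service. The protocol does not link these rates to the planning assumption.

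**The concern.** The proportion of people with a repeat event accumulates over time, so for the same people counted in the same way it cannot be larger at 14 days than at 3 months. A planning value of 10% at 14 days is above a cited value of 7.7% at 3 months. Either the two figures describe different populations or units, which the protocol should say, or the planning value does not belong to the 14-day window.

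The line giving 0.1 does not itself repeat the window, but the sample-size section names no other outcome. A longer window would not help: the longest secondary window is 90 days, which is about the 3 months that the 7.7% covers. If 0.1 did refer to a longer window, the calculation would not be for the primary endpoint.

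At stake is the only planning statement for the primary outcome. If the true baseline is well below 10%, a 5-point fall is a much larger relative effect than the halving it appears to be, or cannot happen at all. The power for a plausible effect would then be lower than the protocol suggests.

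**Working it through.** **Inputs.** From the protocol's sample-size section: 3 clusters, 12 cluster-periods (hence 4 periods), 454/598/323 calls per cluster per quarter, intraclass coefficient 0.1, significance level 0.05 (taken as two-sided; the protocol does not say), baseline 0.10, target 0.05. From the background: 7.7% at 3 months, 17.7% at 6 months.

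**Model.** Standard Hussey–Hughes stepped wedge on cluster-period means: fixed period effects, one random cluster effect, one cluster crossing over at each of periods 2, 3 and 4. With baseline p1 and intervention rate p2, take the pooled variance v = p̄(1 − p̄), where p̄ = (p1 + p2)/2. The between-cluster variance is 0.1v and the cell sampling variance is 0.9v/n. Both scale with v, so for this layout generalised least squares gives SE = 0.0499 × √v. Power = Φ((p1 − p2)/SE − 1.96).

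**The plan's own figures.**
- Call counts: (639,811 + 449,916) × 0.01/24 = 454; (662,745 + 773,066) × 0.01/24 = 598; 774,128 × 0.01/24 = 323. All three reproduce.
- 10% to 5%: v = 0.075 × 0.925 = 0.0694; SE = 0.01315; 0.05/0.01315 = 3.80; power = Φ(1.84) = 96.7%. The difference detectable at 80% power is 3.8 points.
- So 5 points at 80% does not reproduce in this base case. It is approached only under more conservative choices that the protocol does not state. One is 323 calls for every cluster with the full control-rate variance as the cell variance (78.2%); another is a t reference with 4 degrees of freedom (80.8%). On its own inputs the stated difference is conservative.

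**What the cited rates imply for 14 days.**
- In the same population and unit, the 14-day rate is at most 7.7%.
- Under a constant hazard (an assumption), the 3-month figure gives 1 − 0.923^(14/91.25) = 1.22%, and the 6-month figure gives 1 − 0.823^(14/182.5) = 1.48%.
- Conversely, under the same assumption, 10% at 14 days would mean 1 − 0.9^(91/14) = 50% at 3 months.

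**Power by baseline, same design, pooled variance throughout.**

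| Baseline | SE for halving | Power to halve | Detectable at 80% (relative) | A 5-point fall is |
|---|---|---|---|---|
| 10% (plan) | 0.0131 | 97% | 3.8 points (38%) | a 50% reduction |
| 7.7% (cited 3-month rate) | 0.0116 | 91% | 3.3 points (43%) | a 65% reduction |
| 5% (assumed) | 0.0095 | 75% | 2.6 points (53%) | abolition |
| 3% (assumed) | 0.0074 | 53% | 2.0 points (66%) | impossible |
| 1.48% (constant hazard) | 0.0052 | 29% | 1.3 points (86%) | impossible |
| 1.22% (constant hazard) | 0.0048 | 25% | 1.1 points (93%) | impossible |

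Example at 7.7%: p̄ = 0.05775, v = 0.0544, SE = 0.01164, 0.0385/0.01164 = 3.31, power = Φ(1.35) = 91%.

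The planned extract is longer than four quarters. With 8 quarters, power to halve is 96% at 7.7%, 84% at 5%, 62% at 3% and 30–36% at 1.2–1.5%.

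**The case against.** **The 7.7% comes from another service.** A reader might infer that 7.7% is a hard ceiling for this trial, so that 10% is impossible. The protocol does not support that. The figure is Scottish, and the unit may differ: the plan counts calls, and frequent callers raise a call-level proportion above a patient-level one. The eligibility criteria also admit a recorded impression of a diabetic problem, which may widen the case definition. This objection stands. What is shown is an unreconciled discrepancy and an unsourced input.

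**The low baselines are assumed.** A reader might take 1.2–1.5% as the 14-day rate. It rests on a constant hazard, which the cited figures do not fit exactly: 7.7% at 3 months would give 1 − 0.923² = 14.8% at 6 months, not 17.7%. Among those free of recurrence at 3 months, (17.7 − 7.7)/92.3 = 10.8% recur in the next three, so the hazard does not fall between the two quarters. The protocol gives no timing within the first three months, so the low baselines show a range and are not an estimate.

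**Detectability at the low end.** A reader might conclude that at 1.2–1.5% even complete elimination of repeats would be missed. That follows only if the variance is held at the control rate while the rate itself falls to zero. With pooled variance, power to detect abolition is 88–93%.

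**Nothing operational depends on the number.** The roll-out is complete and the data are a fixed routine extract, so no recruitment target would change. Nor does the protocol say that a null result will be read as absence of effect. Both points stand and limit the weight of the finding. They do not remove the need for a planning statement that agrees with the rest of the document.

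**Conclusion.** The point holds in a limited form. The detectable difference for the 14-day primary outcome rests on a 10% baseline that has no source and exceeds the only recurrence rate the protocol cites, 7.7% over a window more than six times as long. A true rate of 10% in this service is not excluded, but the protocol offers no figure for it.

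The damage depends on the true 14-day rate. At 7.7%, power to halve repeats is still 91%, although the stated 5-point fall becomes a 65% relative reduction. At assumed baselines of 5% and 3%, power to halve is 75% and 53%. At 1.2–1.5% it is 25–29%, only near-abolition (86–93% relative) is detectable, and a 5-point fall cannot occur. It would therefore be wrong to infer that the study could not have shown an effect: that describes only the bottom of the range.

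These powers assume the four-period layout, a two-sided 0.05 level, pooled variance, a within-cluster correlation that does not decay over time, and a normal reference. With three clusters, a small-sample t reference would lower all of them.

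**What to change.** Replace 0.1 with the 14-day repeat proportion observed in the service's own records for the 12 months before first introduction. The study-design section says the extract assigns each patient a unique number, so repeats can be counted. State the source and the unit (patients or calls), and reconcile the value with the 3- and 6-month figures in the background. The 2012–2017 data are not a sure alternative: the protocol shows only total attendance counts for those years, scaled by an assumed 1%.

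Then restate the detectable difference and power for the 14-day outcome over a range of baselines, naming the method and the sidedness of the test. If the observed rate is below about 5%, say that a 5-point reduction is not attainable and that the result will be read from the confidence interval.

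The cost is one query on data already being extracted, a wording change, and possibly a less favourable stated figure. The design, intervention and data collection are unaffected.
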